**Figure 1 F1:**
[figure not shown]
**Patient flow through trial**.

### Sample size

A sample size calculation based on detecting a 2 kg difference in weight loss at the 12 week follow-up between any of the planned interventions and comparator group, with 90% power and 5% significance level found that 70 participants randomised to each group will be sufficient. This estimate is based on a standard deviation of 3.2 kg [11,14] and allows for a 20% dropout rate. To enable a more realistic drop-out rate and to get greater precision, 100 participants were allocated to each arm. However, not many general practices or pharmacies were prepared to offer treatment themselves and training places were limited, so that only 70 will be allocated to these arms. A total of 740 participants will be randomized.

### Planned analysis

Both between and within group analyses for primary and secondary outcomes at programme end and 12 months will be performed according to intention to treat. Participants in whom weight at follow up is not available will be assumed to have their baseline weight. However, sensitivity analysis will also be undertaken, assuming follow up weight to be the last recorded weight.

As the outcomes are all measured on a continuous scale (weight loss, percentage weight loss, self-reported physical activity), differences between intervention group and the comparison (minimal intervention) group will be investigated using least squares linear regression. Between group analyses will be expressed as both unadjusted and adjusted differences (corrected for baseline score and covariates of age, gender, ethnicity and educational level). A secondary analysis will compare the outcomes of the commercial weight loss programmes (Weight Watchers, Slimming World and Rosemary Conley) with the primary care programmes (general practice and pharmacy-based interventions). Data on choice of programme, number of sessions attended and reasons for drop-out will be presented using descriptive statistics.

To determine whether the service reaches those most in need, the age, gender, and deprivation score (derived from the postcode of residence) of those who were randomised will be compared to those who received the letter but did not respond or declined to be randomised.

Responses to open-ended questions about experience of the service and reasons for dropping out of their allocated programme will be categorised and presented descriptively.

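### Setting missing weights to zero change makes the arms' variances unequal, so the least-squares comparisons should state robust or arm-specific standard errors (low severity, no cost)

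*Protocol article*

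**What the plan says.** Two choices in the Planned analysis section of the protocol article meet here. The main rule for missing outcomes is "Participants in whom weight at follow up is not available will be assumed to have their baseline weight", at programme end and at 12 months; carrying the last recorded weight forward is the sensitivity analysis. Differences from the comparator "will be investigated using least squares linear regression", both unadjusted and adjusted for baseline and four covariates.

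The article does not say whether one model holds all eight arms or each programme is regressed separately against the comparator. Nor does it say whether standard errors are model-based or robust. The Sample size section uses one SD for all arms: "This estimate is based on a standard deviation of 3.2 kg [11,14] and allows for a 20% dropout rate". It then sets 100 per arm because more dropout is expected, with 70 in the general practice and pharmacy arms.

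**The concern.** Ordinary least-squares standard errors use one residual variance for every arm in the model. The zero-change rule turns each arm into a mixture: some participants at exactly zero and the rest spread around the arm's mean loss. The further that mean lies from zero, the larger the variance of the mixture. The plan's own missing-data rule therefore produces unequal variances between effective and less effective programmes, even with fully independent participants and a common SD among those weighed.

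The trial is meant to help a commissioner choose services. If the spread of the successful programmes is pooled into the standard error of a modest programme's contrast, that programme's interval becomes too wide, while the intervals of the strong programmes stay about right.

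**Working it through.** **The plan's own figure.** With a 2 kg difference, SD 3.2 kg, two-sided 5% (sidedness assumed) and 90% power, n = 2 × (1.960 + 1.282)² × 3.2² / 2² = 53.8, so 54 per arm; 54 / 0.8 = 67.5, so 68 (69 with a t-based count). The stated 70 is reproduced, and 6 × 100 + 2 × 70 = 740.

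**Variance under the zero rule.** Let d be the share missing, m the mean loss among those weighed and s their SD. Then

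variance = (1 − d)s² + d(1 − d)m².

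**Inputs.** From the article: s = 3.2 kg (taken as the SD among those weighed), d = 0.20 and the arm sizes. Assumed: the mean losses, since the article gives none by arm; d equal in all arms; d = 0.31 and 0.45 as sensitivity values. In the Background, 31% is the low end of the loss to follow-up cited from trials of at least two years, and the cited UK trial followed up 54% at 12 months, a loss of 46%.

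**One eight-arm model, worked at d = 0.20.** Comparator 1 kg; Size Down, general practice and pharmacy 2 kg; commercial and choice arms 5 kg.
- Comparator: 0.8 × 10.24 + 0.16 × 1 = 8.352
- Weaker arms: 8.192 + 0.16 × 4 = 8.832
- Stronger arms: 8.192 + 0.16 × 25 = 12.192
- Pooled: (99 × 8.352 + 99 × 8.832 + 396 × 12.192 + 138 × 8.832) / 732 = 10.585
- Size Down v comparator: correct SE = √((8.352 + 8.832)/100) = 0.4145; pooled SE = √(10.585 × 0.02) = 0.4601; ratio 1.11
- Commercial v comparator: correct SE = √((8.352 + 12.192)/100) = 0.4533; ratio 0.4601/0.4533 = 1.015

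Excess in the Size Down SE, with the stronger programmes' excess in brackets:

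| Missing | Losses 1 / 2 / 4 kg | Losses 1 / 2 / 5 kg | Losses 2 / 3 / 4 kg |
|---|---|---|---|
| 20% | 6.8% (1.3%) | 11.0% (1.5%) | 4.7% (1.7%) |
| 31% | 10.2% (1.9%) | 16.2% (2.1%) | 6.9% (2.4%) |
| 45% | 14.0% (2.5%) | 22.2% (2.7%) | 9.2% (3.2%) |

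(Order: comparator / weaker / stronger.) The 70-person arms are close to Size Down: 6.6%, 10.7% and 4.4% at 20% missing. Coverage of the Size Down interval is 96-97% at 20% missing and at most about 98% at 45%.

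**Power.** Take a 2 kg difference among those weighed (comparator 1 kg, weaker arms 3 kg, stronger arms 4.5-5 kg). At 20% missing, Size Down power falls from 96.5% to about 95%, and power of the 70-person arms from 92.5% to about 90%. At 31%, Size Down falls from 92.8% to 88-89%; at 45%, from 84% to 74-76%.

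**Separate two-arm models.** With 100 v 100 and equal d, the pooled and arm-specific SEs are identical. With 70 v 100, the smaller arm has the larger variance but the smaller weight in the pool. At d = 0.20, m = 3 v 1 kg: pooled variance = (69 × 9.632 + 99 × 8.352)/168 = 8.878; SE = √(8.878 × (1/70 + 1/100)) = 0.4643; correct SE = √(9.632/70 + 8.352/100) = 0.4702; ratio 0.987. With the comparator at 1 kg, 2-3 kg in the 70-person arm and 20-45% missing, the SE is too small by about 0.5-3%. The extreme case of 45% missing and 5.9 v 1 kg gives 0.929.

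**Arm-specific variances.** Simulated coverage was 94.5-95.1% for every programme in four scenarios with 50-80% followed up.

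All figures are for the unadjusted comparison.

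**The case against.** The strongest reply is that least squares fixes the estimate, not the standard error. Robust errors are compatible with the stated method, and a condensed article may leave that choice, and the model layout, to an analysis plan that is not shown. The wording about each intervention against the comparison group fits pairwise models at least as well as one joint model, and pairwise 100 v 100 contrasts show no error at equal missingness. This stands: the point is conditional, and the article makes no equal-variance statement that could be called wrong. What remains is that the article does fix the combination of zero imputation and unqualified least squares, and that combination produces unequal variances under either layout.

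A reader might infer that the intervals are simply wrong, or that programmes will falsely appear effective. The documents do not support either. In the eight-arm model the affected intervals are too wide, hence conservative. A reader might also infer a collapse in power. Falls such as 34% to 20-25% for Size Down need 45% missing together with a 1 kg difference among those weighed, half the design's 2 kg.

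Missingness of 31-45% is also not established for the three-month endpoint. Those figures come from follow-up of a year or more, and the plan offers home visits and then accepts self-reported weight before zero is imputed. The article does, however, expect dropout above 20%, and the zero rule also applies at 12 months.

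If missingness differs between arms, small departures the other way are possible. With poor follow-up only in the general practice and pharmacy arms (50% against 80% elsewhere), coverage for the commercial arms in the joint model was 94.5%.

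**Conclusion.** The point holds in conditional form, at low severity. Zero imputation makes arm variances differ. With ordinary standard errors in one eight-arm model, weaker-programme intervals are too wide by roughly 4-11% at 20% missing and up to about 22% at 45%, at a modest cost in power and with little effect on the strongest programmes. With separate models, only the 70 v 100 contrasts are touched, usually by no more than 3%. The sizes rest on assumed mean losses, equal missingness across arms and 3.2 kg as the SD among those weighed. Unequal variance does not bias the estimated differences; whether zero change is a credible assumption for missing weights is a separate question.

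**What to change.** Keep the least-squares regression and the adjustment set. Add one sentence to the analysis plan: all between-arm contrasts in weight loss and percentage weight loss, at three months and one year, use heteroscedasticity-consistent (HC3) or arm-specific-variance standard errors. The same sentence can state whether one model or separate models are fitted. The cost is one software option, with no material loss at 70-100 per arm; no change to sample size or data collection is needed.

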The participants allocated to the commercial operators Weight Watchers [20], Slimming World [21] and Rosemary Conley [22] have a choice of programme locations and times. Commercially, these programmes run continuously, with no set number of sessions and no fixed starting date. People who are not participating in the trial pay fees to attend these programmes and these people attend alongside those in the trial, for whom treatment is free. Each programme is provided in accordance with the respective organisations' guidance and the group leaders are trained by the organisations. The vouchers provided to trial participants exempts them from payments for the first 12 weeks of the programme. Thereafter, if participants wish to continue attending sessions they are required to pay the appropriate fees to the service provider. The Size Down Programme is an NHS group-based programme in which all members of the group commence together and follow a prescribed course of sessions. It takes place in various community venues. Participants randomised to the general practice or pharmacy arms attend one-to-one sessions in the general practice or pharmacy. Appointments are made at a time mutually convenient to the participant and the nurse/pharmacist.

In the choice arm, participants are able to choose from any of the intervention programmes described above.

Participants allocated to the comparator group are sent vouchers for 12 free sessions to attend a local authority run leisure centre (typically including an exercise room, swimming pool, and other facilities such as squash or badminton courts). Participants are not given an appointment to attend and are given no dietary or individual physical activity advice and support. It is acknowledged that weight loss can occur with exercise-only, but effects are modest [8,23].

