### Data collection

#### Baseline data

Data collected at baseline by the call centre, prior to randomisation includes: demographic data, information on previous use of weight loss programmes including commercial services, current physical activity levels (using the International Physical Activity Questionnaire-short form (IPAQ-short)) [24] and use of weight loss medication. Patients allocated to the choice arm are asked about their reasons for choosing their programme.

When participants attend their first weight-loss session in the six interventions, the leader/counsellor measures participants' height and weight. Scales are validated by the research team using standardised weights, unless evidence of recent independent validation is provided. The commercial providers often use self-reported height, so this will be re-measured at follow-up by the blinded assessor. People in the comparator control group and people who are randomised but who do not attend their allocated programme are contacted and a researcher makes an appointment to measure height and weight.

During the 12-week programmes the service providers record weights on each visit. The comparator group are weighed at baseline only.

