#### Outcome assessment

The primary outcome is weight loss at three months follow-up. The secondary outcomes are self-reported physical activity using the IPAQ-Short version, weight loss at one year and percentage weight loss at 3 months and one year.

At three months after programme start (programme end) the service providers weigh participants. Participants who are no longer attending their allocated programme are contacted and offered follow-up at home or another convenient location. If participants decline to be followed-up in person, they are asked to provide a self-reported weight, which is recorded as self-report. In addition, the IPAQ-short is administered by phone and participants who have dropped out of their allocated programme are sent an open-ended question asking for their views about the weight loss programme to which they were allocated.

The final outcome assessment takes place one year after randomisation. In addition to assessment of their BMI, participants are asked to complete the IPAQ-Short, their opinion of the service and whether they have tried any other weight loss programmes or strategies over the course of the year. Participants are invited to attend their general practice for a brief appointment, where the practice nurse or a health trainer who is blind to the allocation arm, undertake follow up measures. Participants unable to attend their general practice will be offered home visits for measurements. If height has not been measured previously, it is assessed using a Leicester height measure. Participant flow through the trial is shown in figure 1.

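### At 3 months the only named sensitivity analysis for missing weights can move the programme arms but not the comparator, so it cannot test the baseline-weight rule

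*Protocol article*

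**What the plan says.** Two rules for missing weights are fixed in the Protocol article, Planned analysis. The primary one is "Participants in whom weight at follow up is not available will be assumed to have their baseline weight". The only alternative named is a "sensitivity analysis will also be undertaken, assuming follow up weight to be the last recorded weight".

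What counts as the last recorded weight depends on the arm. Under Data collection, Baseline data: "During the 12-week programmes the service providers record weights on each visit", and, for the control arm, "The comparator group are weighed at baseline only".

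The route to the 3-month weight also differs. Under Outcome assessment, "At three months after programme start (programme end) the service providers weigh participants". Comparator participants have leisure-centre vouchers and no provider; under Interventions, "Participants are not given an appointment to attend and are given no dietary or individual physical activity advice and support". The same section does not expect zero change in that arm: "It is acknowledged that weight loss can occur with exercise-only, but effects are modest".

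There is a retrieval step for people who stop attending: "Participants who are no longer attending their allocated programme are contacted and offered follow-up at home or another convenient location". Those who decline a visit are asked for a self-reported weight.

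**The concern.** A sensitivity analysis is useful if it varies the assumption that could be wrong. Here the assumption is zero loss for everyone who is missing, in both arms of each contrast. At 3 months the alternative rule changes that assumption for programme attenders only. For a missing comparator participant the last recorded weight is the baseline weight, so the second analysis repeats the first.

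Two things are at stake. First, the check has a built-in direction: if people lose weight while attending, it can only enlarge the apparent benefit. Second, if the two analyses agree, the agreement will look like robustness although both rest on the same untested zero in the comparator. These contrasts are meant to guide which services the Primary Care Trust contracts (Background), so a check that tests one side only is a weak support for them.

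**Working it through.** **Inputs from the documents (Sample size).** Target difference 2 kg at 12 weeks, each programme against comparator; SD 3.2 kg; 90% power; 5% significance; 20% drop-out, a single rate for all arms; 100 per arm (70 in the general practice and pharmacy arms).

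**Assumptions, not in the documents.** Missing shares by arm, mean losses, and the on-programme loss of those who go missing. Ranges are shown.

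**1. The plan's own figure.** n per group = 2 × (1.960 + 1.282)² × 3.2² / 2² = 53.8, so 54. Allowing for 20% drop-out, 54 / 0.8 = 67.5, so 68 (69 with the t distribution). The stated 70 reproduces, and 2 kg, 3.2 kg and 20% are fair yardsticks.

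**2. What each rule estimates at 3 months.** Let m_P and m_C be the missing shares in programme and comparator, μ_P and μ_C the mean losses of those weighed, and L the mean loss at the last recorded visit among missing programme participants (never-attenders count as zero).

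- Baseline rule: D_B = (1 − m_P)μ_P − (1 − m_C)μ_C
- Last-weight rule: D_L = D_B + m_P × L + m_C × 0
- Movement: D_L − D_B = m_P × L, with nothing from the comparator

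| Programme missing | L = 0.5 kg | L = 1 kg | L = 2 kg | L = 3 kg |
|---|---|---|---|---|
| 20% | 0.10 | 0.20 | 0.40 | 0.60 |
| 30% | 0.15 | 0.30 | 0.60 | 0.90 |

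At 20% missing this is 5% to 30% of the 2 kg target.

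**3. No true difference, equal missingness, L equal to the common mean loss.** The baseline rule gives 0. The last-weight rule gives the following; rejection rates come from 20,000 simulated two-arm trials, 100 per arm, SD 3.2 kg, SD of carried-forward losses 1.6 kg, missing at random within arm.

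- 20% missing: +0.2 kg at 1 kg lost (about 8% false positives), +0.4 kg at 2 kg lost (about 16%)
- 30% missing: +0.3 kg (about 12%), +0.6 kg (about 33%)

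**4. What the check cannot show.** If missing comparator participants truly lost c kg, both analyses understate the comparator's loss by m_C × c. At 20% missing and c of 1–2 kg that is 0.2–0.4 kg, identical in the two.

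**5. The baseline rule with no true difference.** With μ_P = μ_C = μ, D_B = (m_C − m_P)μ. The per-arm variance of one value, with p the share observed, is p × 3.2² + p(1 − p)μ². For 10% missing in the programme and 30% in the comparator, n = 100 per arm:

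- μ = 1 kg: bias 0.20 × 1 = 0.2 kg; SE = √((9.306 + 7.378)/100) = 0.408; false-positive rate about 8%
- μ = 2 kg: bias 0.20 × 2 = 0.4 kg; SE = √((9.576 + 8.008)/100) = 0.419; about 16%
- Shares reversed (30% programme, 10% comparator): −0.2 and −0.4 kg
- Equal shares, or μ = 0: no bias, 5%

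**6. With a true 2 kg effect (3 kg v 1 kg, missing like those observed) and L = 2 kg.**

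| Missing, programme v comparator | Baseline rule | Last-weight rule |
|---|---|---|
| 20% v 20% | 0.8×3 − 0.8×1 = 1.6 | 1.6 + 0.2×2 = 2.0 |
| 10% v 30% | 0.9×3 − 0.7×1 = 2.0 | 2.0 + 0.1×2 = 2.2 |
| 30% v 10% | 0.7×3 − 0.9×1 = 1.2 | 1.2 + 0.3×2 = 1.8 |

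The last-weight figure can be nearer the truth or further from it. What is constant is that it moves one way only and takes no information from the comparator.

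**The case against.** **Retrieval reduces the amount missing.** Leaving a programme is not the same as lacking a weight: visits and self-report come first, so imputation applies only to those left over. Never-attenders have no on-programme weight and gain no credit. Both points stand. They lower m_P and L but leave the one-sidedness intact.

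**The asymmetry is not general.** At one year a comparator participant may have a 3-month weight to carry forward, and the one-year assessment is described in the same way for all arms. The planned commercial versus primary care contrast has visit weights on both sides. An individual whose last weight was a gain moves the other way. All of this stands, so a reader who infers that every contrast at every time point is tilted, or that one year must be worse, goes further than the documents allow.

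**The baseline rule is not shown to favour the programmes.** A reader might infer that the missing appointment makes the comparator harder to re-weigh and so inflates the effect. The different follow-up routes make that possible, but no section forecasts unequal loss, and a researcher arranges to weigh comparator participants at baseline, so they can be reached. With equal loss the rule only shrinks a true effect; with more programme loss it works against the programmes.

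**Large figures can be built, but only by stacking assumptions.** With 40% missing in both arms, 2 kg lost at drop-out and all of it regained, and 2 kg kept off by missing comparator participants, the last-weight bias is 0.40 × 2 + 0.40 × 2 = 1.6 kg. Half of that is comparator zeros, which the primary rule shares. A false-positive rate near 41% under the baseline rule needs 4 kg lost in both arms and 30% v 10% missing, which sits badly with the protocol's view that exercise-only effects are modest.

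**An unseen analysis plan may add more.** It may, and silence on further analyses is no fault. The point concerns the one analysis that the article does fix.

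**Conclusion.** The point holds for the 3-month primary endpoint and the programme-versus-comparator contrasts. The named sensitivity analysis cannot test the primary rule where the comparator is concerned, because the two rules coincide there. This follows from the text and needs no unequal drop-out. Its movement is m_P × L, generally towards the programmes: 0.4 kg at 20% missing and 2 kg lost, and 0.1–0.6 kg for losses of 0.5–3 kg. The 20% is the protocol's drop-out allowance and the losses are assumptions.

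The part about the baseline rule is conditional. It is not guaranteed conservative for a between-arm difference: a spurious 0.2–0.4 kg and about 8–16% false positives at 30% v 10% missing with 1–2 kg lost in both arms. It is unbiased under no effect when missingness is equal, and its sign follows whichever arm loses more people. The documents do not support the wider conclusion that the primary analysis is invalid or that every planned analysis is biased. The change is worth making because it is cheap and gives a robustness check that can disagree with the primary result in either direction.

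**What to change.** Baseline weight may stay as the primary rule if comparability with other trials is wanted. Change the sensitivity analyses in Planned analysis:

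- Replace the last-recorded-weight analysis as the sole check, or keep it as supplementary with a statement that at 3 months it can alter the programme arms only.
- Add multiple imputation (or a likelihood-based model) under missing-at-random, using variables collected in every arm: baseline weight, age, gender, ethnicity and education. Feeding in visit weights or attendance would bring back part of the asymmetry, since the comparator has neither.
- Add a delta-adjusted (tipping-point) analysis in which missing participants are made heavier than imputed, for example by 0 to 3 kg, with the shift varied separately in programme and comparator arms.
- Report the number and share of missing weights by arm at 3 months and one year.

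The cost is analysis wording and modest programming, with no new data. The downside is a little more analysis work and results somewhat less comparable with trials that report last weight carried forward.

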**Programme Characteristics**	**Weight Watchers**	**Slimming World**	**Rosemary Conley**	**NHS Size Down**	**General practice/pharmacy**

Group or individual	Group. 1-2-1 for new members and when weighed. Group talk from leader with discussion.	Group. 1-2-1 when weighed. Group used to share progress and lapses and to find and share solutions.	Group. 1-2-1 when weighed and to establish calorie allowance. Also, additional support available via email/telephone 1-2-1.	Group. Group used to share progress and lapses and to find and share solutions. All group members start in same week and progress as a closed group.	Individual

Duration of sessions, frequency, programme length and setting	1 hour sessions. 12 weekly sessions provided as part of Lighten Up. Community based venues.	1 1/2 hour sessions. 12 weekly sessions provided as part of Lighten Up. Access to website, magazines and 1-2-1 telephone support from consultant or other members. Community based venues.	1 1/2 hours 12 weekly sessions provided as part of Lighten Up. Community based venues.	2 hour duration; groups weekly × 6 weeks; drop-in at 9 and 12 weeks. Community based venues. All group members start in same week and progress as a closed group.	1^st ^session 30 minutes, follow up sessions 15-20 minutes 12 weekly sessions provided as part of Lighten Up - although may not have taken place weekly in all cases. In surgery or pharmacy.

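### The planned least squares analysis and the sample size treat participants as independent although several programmes are delivered in shared groups or by few providers, so precision is overstated if outcomes within groups or providers correlate

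*Protocol article*

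**What the plan says.** **Analysis.** Under Planned analysis the article states that "differences between intervention group and the comparison (minimal intervention) group will be investigated using least squares linear regression". Differences are reported unadjusted, and adjusted for baseline score, age, gender, ethnicity and education. A secondary analysis sets the three commercial programmes against the general practice and pharmacy programmes. No group, leader, practice or pharmacy effect is named.

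**Sample size.** The calculation is "based on detecting a 2 kg difference in weight loss at the 12 week follow-up", "with 90% power and 5% significance level found that 70 participants randomised to each group will be sufficient". The text adds: "This estimate is based on a standard deviation of 3.2 kg", and it "allows for a 20% dropout rate". It then says that "100 participants were allocated to each arm", with general practice and pharmacy held at 70, for a total of 740. No ICC or design effect appears.

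**Delivery.** Patients are randomised individually (Methods/Design). Table 1 shows four group programmes, and for Size Down it says: "All group members start in same week and progress as a closed group". General practice and pharmacy support is one-to-one, but Sample size reports that "not many general practices or pharmacies were prepared to offer treatment themselves" and that training places were limited. Comparator participants receive leisure-centre vouchers, with no appointment and no advice (Interventions).

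**The concern.** People who share a closed group, a leader or a counsellor share part of their treatment. Table 1 makes group exchange of progress and solutions part of Size Down and Slimming World. For general practice and pharmacy it lists client-led sessions, no fidelity checking, and sessions that may not always have been weekly, so differences between providers are to be expected. The comparator has no such structure. This is a partially nested design: residuals can be correlated in the programme arms and independent in the comparator.

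Least squares with its usual standard errors assumes independent residuals with one common variance. If the within-cluster correlation is positive, it understates the uncertainty of the affected contrasts. The secondary commercial-versus-primary-care comparison is more exposed because both sides are nested. The results are meant to guide which services the Primary Care Trust contracts, and the NHS-delivered arms, where clustering is most plausible, bear directly on that decision.

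**Working it through.** **Inputs from the article:** difference 2 kg, SD 3.2 kg, 5% significance (taken as two-sided), 90% power, 20% dropout; 100 per arm, 70 in general practice and in pharmacy.

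**Assumed, because the article gives neither:** ICC 0.02 to 0.10, and m = 5 to 10 trial participants per group or provider.

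**1. Reproduce the stated 70.** n = 2 × [3.2 × (1.960 + 1.282) / 2]² = 53.8, so 54 evaluable per arm. Dividing by 0.8 gives 67.5, so 68 randomised. The t-based version gives 55, then 69. The one-sided version gives 44, then 55, which does not fit. The stated 70 therefore matches a two-sided calculation under independence, with almost nothing to spare for a design effect.

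**2. Design effect in a programme arm.** DE = 1 + (m − 1) × ICC.
- Low: 1 + 4 × 0.02 = 1.08
- Central: 1 + 9 × 0.05 = 1.45
- High: 1 + 9 × 0.10 = 1.90

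**3. Standard error and type I error.** With an unclustered comparator and equal total variance:

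SE true = 3.2 × √(DE/n_prog + 1/n_comp); SE naive is the same with DE = 1; ratio = SE true / SE naive; type I error of the naive test = 2 × [1 − Φ(1.96 / ratio)].

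| Arms | DE | SE naive (kg) | SE true (kg) | Ratio | Type I error |
|---|---|---|---|---|---|
| 100 v 100 | 1.08 | 0.453 | 0.462 | 1.020 | 5.5% |
| 100 v 100 | 1.45 | 0.453 | 0.501 | 1.107 | 7.7% |
| 100 v 100 | 1.90 | 0.453 | 0.545 | 1.204 | 10.4% |
| 70 v 100 | 1.08 | 0.499 | 0.510 | 1.023 | 5.5% |
| 70 v 100 | 1.45 | 0.499 | 0.561 | 1.125 | 8.1% |
| 70 v 100 | 1.90 | 0.499 | 0.617 | 1.237 | 11.3% |

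For 100 v 100 the true SE is 2% to 20% larger than the naive SE. Put the other way, the naive SE is too small by 1 − 1/ratio, which is 2% to 17%.

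**4. Power for 2 kg after 20% dropout.** Power = Φ(2 / SE true − 1.96), holding the design effect fixed.

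| Arms | No clustering | DE 1.08 | DE 1.45 | DE 1.90 |
|---|---|---|---|---|
| 80 v 80 (100-participant arms) | 97.7% | 97.2% | 94.7% | 90.7% |
| 56 v 80 (general practice, pharmacy) | 94.8% | 93.9% | 89.1% | 82.7% |

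**5. Commercial (300) v primary care (140), both sides nested.** Take ICC 0.05 with m = 5 on the commercial side and 10 on the primary care side. The design effects are 1.20 and 1.45, the SE ratio is 1.171 and the type I error is 9.4%. With m = 2 on the commercial side the figures are 1.150 and 8.8%.

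**6. Sensitivity to cluster size.** For 100 v 100 with m = 2 to 3 and ICC 0.02 to 0.10, the type I error is 5.1% to 6.2%. With m = 20 and ICC 0.10 it reaches 16.1%, or 17.8% for 70 v 100.

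**The case against.** **The effect is not uniform.** Commercial participants choose among venues and times, those groups run continuously with no fixed start, and trial participants sit among fee-paying members. A hundred people spread in this way may leave only two or three per group, where step 6 shows little harm. The choice arm is spread over six programmes. Non-attenders and the imputation of baseline weight dilute any correlation further. All of this stands. A reader might infer that the standard error of every programme-versus-comparator contrast is materially too small; the article does not support that.

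**The power is mostly protected.** A reader might also infer that power falls well below 90% throughout, by applying the design effect to 70 v 70 (56 v 56 after dropout: 84.8% at DE 1.45). No such contrast is planned, because the comparator has 100. Five of the seven programme arms have 100 and keep at least 90.7% over the assumed range. This also stands.

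**A fuller plan may deal with it.** Least squares names an estimator, robust standard errors are compatible with it, and a condensed article may leave the variance method to an analysis plan that is not shown. This stands in part. It cannot be said that the trial will ignore clustering. But the article does fix a model, a covariate list and a sample size, all three treat participants as independent, and the same article describes the shared delivery.

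**Conclusion.** The point holds in a conditional form. As stated, the analysis and the sample size make no allowance for clustering by group or provider. Whenever that correlation is positive, intervals are too narrow and p-values too small.

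The direction follows from the design; the size rests on an assumed ICC and cluster size. Over the assumed range the nominal 5% test runs at about 5.5% to 10% for 100 v 100, and the central case gives 7.7%, or 8.1% for a 70-participant arm. For general practice and pharmacy, power is 93.9% to 82.7%. The concern is strongest for Size Down, general practice, pharmacy and the secondary commercial-versus-primary-care comparison, and it may be negligible for the commercial and choice arms.

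**What to change.** - **Record the cluster.** For each participant, take the group, leader, practice or pharmacy attended from provider records. The call centre's bookings will not be enough, because general practice and pharmacy participants arrange their own first session.
- **Change the model.** Use a partially nested mixed model: a random group or provider effect in the programme arms, none in the comparator, arm-specific residual variance and small-sample degrees of freedom. Alternatively, keep least squares with cluster-robust standard errors and a small-sample correction, which matters where providers are few.
- **Define membership.** Treat comparator participants and non-attenders as singletons. Place choice-arm participants in the group or with the provider they attended.
- **Qualify the sample size.** State that 90% power at 70 per group assumes no clustering, or restate it with an assumed ICC and cluster size.

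The cost is one more identifier to collect, a little more data handling, changed model wording and slightly wider intervals. If the ICC is near zero, the results will barely change.
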